### Recruitment

The trial will recruit a total of 120 participants through local, media, and social advertisements, posters, and informative talks. All participants will be informed about the purpose, procedures, benefits, and risks associated with participation in the study before signing a written consent form.

### Participant inclusion and exclusion criteria

The inclusion criteria will be the following: (1) individuals aged 60 to 75 years old; (2) fluency in Spanish language (both written and spoken); (3) ability to walk independently; (4) physical capability to engage in an exercise program; (5) competence in using a smartphone and mobile applications without assistance.

Participants meeting any of the following criteria will be excluded from the study: (1) individuals with a history of acute or terminal illness, as well as those who have experienced myocardial infarction, coronary artery bypass grafting, angioplasty, angina, or other cardiac conditions within the past year; (2) uncontrolled medical problems that the physician believes would preclude them from participating in an exercise program, such as acute systemic illness (*e.g.,* pneumonia), acute rheumatoid arthritis, and acute or unstable heart failure; (3) conditions requiring a specialized exercise program such as uncontrolled epilepsy, significant neurological disease or impairment, inability to maintain an upright seated position or unable to move independently, multiple sclerosis, cancer, Parkinson’s, Alzheimer’s, or chronic obstructive pulmonary disease; (4) uncontrolled hypertension diagnosed by a physician; (5) type I diabetes or uncontrolled type II diabetes; (6) history of major psychiatric illness (*e.g.,* schizophrenia, generalized anxiety disorder, or depression according to the DSM-5); (7) morbid obesity (body mass index > 39.9); (8) having experienced three or more self-reported falls in the last year; (9) not living in the community (i.*e.,* residing in nursing homes); (10) participation in an exercise program within the preceding six months; (11) having been diagnosed with COVID-19 with hospitalization in intensive care unit; (12) any other condition that could interfere with the study purposes and pose a risk to the participant, as determined by the researcher and physician. Eligibility criteria will be verified by a physician and a member of the research team during telephone screening and in the initial assessment. A medical history and the PAR-Q (Physical Activity Readiness Questionnaire) will be administered at the initial assessment.

Criteria for discontinuing intervention for a given trial participant include participant request, disease onset or worsening impairing research results or affecting exercise capacity, etc.

### Randomization and blinding

The randomization will be performed by a researcher not involved in the study. The allocation sequence will be determined by a computer-generated list (http://www.randomizer.org/). If a couple living in the same house participates, both will be randomized into the same group [37]. Blinding of the intervention is impossible for participants and therapists administering the intervention given its nature (*i.e*., exercise training). During the intervention, subjects will not be told about the existence of groups with and without motivational strategies. Statisticians and assessors in charge of outcome assessments will be blinded to participants’ allocation.

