**Fig. 2 Fig2:**
[figure not shown]
Flowchart of the study protocol. CON: Control group, SUP: Supervised exercise without motivational intervention, SUP + : Supervised exercise with motivational intervention, UNSUP: Unsupervised exercise without motivational intervention, UNSUP + : Unsupervised exercise with motivational intervention

The study will be conducted at the University of Castilla-La Mancha (Spain). It will be reported in accordance with the Consolidation Standards of Reporting Trials (CONSORT) statements for cluster RCTs and Standard Protocol Items: Recommendations for Interventional Trials [36].

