*LB* Lower-body, *RIR* Repetitions in reserve, *RPE* Rate of perceived exertion, *UB* Upper-body

*1- Control group (CON)*

Participants will not perform any other exercise program during the intervention period and will be advised to maintain their usual lifestyle.

*2- Supervised exercise without motivational intervention (SUP)*

The SUP group will participate in an exercise program conducted at university facilities in small groups (≤ 8 participants per session) under the supervision of a sports scientist. The program will be conducted with the equipment usually available at a gym (*i.e.,* weight machines, dumbbells, kettlebells, discs, pulleys, elastic bands, and stationary bicycles).

*3- Supervised exercise with motivational intervention (SUP +)*

The SUP + group will receive the same exercise program as the SUP group (Table 1) but with motivational strategies based on self-determination theory designed to increase participants’ perception of autonomy, competence, and relatedness. These strategies will be based on 6 colors simulating martial arts levels, from white belt (beginner) to black belt (advanced). Each level will employ different strategies to achieve the specific objectives set for that level. Motivational strategies include telephone calls, educational infographics, workshops and videos about exercise benefits, motivational messages before and after each training session, and reports of the results obtained in the mid-intervention assessment. More details about the motivational strategies are available in Supplementary Table 4.

*4- Unsupervised exercise without motivational intervention (UNSUP)*

The UNSUP group will complete an unsupervised exercise program prescribed via a mobile app designed for at-home use without face-to-face supervision. The program will involve exercises that target the same muscle groups and movements as the supervised groups but are adapted to be performed at home using elastic bands and participants’ body weight.

*5- Unsupervised exercise with motivational intervention (UNSUP +)*

The UNSUP + group will receive the same exercise program as the UNSUP group (as detailed in Table 2), plus equivalent motivational strategies to those administered to the SUP + group. More information is available in Supplementary Table 4.

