### Statistical analysis

Data will be preferentially presented as mean ± standard deviation or as proportions for continuous and categorical variables, respectively. Data normality will be assessed by the Kolmogorov–Smirnov test and will be log-transformed in case of non-normal distribution. Baseline differences will be assessed through a one-way ANOVA. A two-way mixed ANCOVA (group [*i.e.*, CON, SUP, SUP + , UNSUP, and UNSUP +] x time [*i.e.,* baseline, mid, post-intervention, and follow-up assessments]) will be performed, adjusting for baseline values as well as for any other sociodemographic/descriptive variables that may differ between groups (*e.g.,* age, sex). Subsequent post-hoc tests will be conducted to determine which groups significantly differ. Effect sizes will be calculated to assess the magnitude of the differences [87]. Falls and fall-related injuries will be presented as rates/person (ITT analysis) and rates/person/year (± 30 days; PP analysis), and as numbers. Adverse events and dropouts will be compared between groups through Chi-squared tests. Differences in adherence rates will be analyzed using an ANOVA test. Correlation analyses will be used to assess associations between motivators, barriers, and adherence to exercise sessions. Whenever possible, statistical analyses will be performed on an intention-to-treat (ITT) basis (including all randomized participants). The potential effects of missing values and dropouts will also be explored using multiple imputation and sensitivity analyses [88]. As recommended, a complementary per protocol (PP) analysis will be performed (*i.e.,* including only those participants with valid data for baseline and post-intervention assessments and an adherence to exercise program of at least 80%) [89]. SPSS version 24.0 (IBM Corp., Armonk, NY) will be used for statistical analysis, and the significance level will be set at p ≤ 0.05 for all tests.

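### Cohabiting couples are allocated as a unit, but the named tests treat every participant as independent; if couples enrol and their outcomes correlate positively, standard errors will be too small

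*Protocol article*

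**What the plan says.** Three parts of the protocol article bear on this point.

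- **Allocation.** The Randomization and blinding section sets the rule "If a couple living in the same house participates, both will be randomized into the same group". Everyone else is allocated individually.
- **Reporting standard.** The Study design section calls the trial randomised and parallel. Below the Figure 2 caption it says that reporting will follow the "Consolidation Standards of Reporting Trials (CONSORT) statements for cluster RCTs".
- **Analysis.** The Statistical analysis section plans a two-way mixed ANCOVA (five groups by four time points), "adjusting for baseline values as well as for any other sociodemographic/descriptive variables that may differ between groups". For adherence it says "Differences in adherence rates will be analyzed using an ANOVA test". Adverse events and dropouts go to chi-squared tests.

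No household term, random effect between people or cluster-robust error appears. The Sample size section mentions neither an intraclass correlation nor a design effect.

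The Trial groups section adds that the SUP programme is "conducted at university facilities in small groups (≤ 8 participants per session) under the supervision of a sports scientist", and that SUP+ receives the same programme. The two unsupervised arms train at home.

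**The concern.** When both partners always land in the same arm, any positive correlation between them adds to the variance of that arm's mean. A test that counts them as two independent people does not see this. Its standard error is too small and its p-value too low.

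The word mixed in the planned ANCOVA does not help. It refers to a between-group factor crossed with time within a person, so it handles repeated measures on one participant and not correlation between two participants. The covariates are baseline values and descriptive variables. The planned sensitivity analyses address missing values and dropouts.

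Adherence, a primary outcome, is the most exposed. Partners share routines, and in the unsupervised arms they would exercise in the same home. The named tests also cover lower-body muscular function and adverse events, so three of the four primary outcomes are touched.

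**Working it through.** **The plan's own figure.** The Sample size section states 100 participants before dropout (alpha 0.05, power 0.80, five groups, standardised difference 0.43). The noncentral F formula for a group-by-time interaction with independent participants, using f = 0.43/2 = 0.215, four measurements and a repeated-measures correlation of 0, gives power 0.814 at N = 100 and 0.787 at N = 95. So 100 is reproduced with no cluster term. The match depends on that unstated correlation; at 0.5 the same formula gives 55.

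**Inputs for the check.** The article gives neither the share of participants in couples (c) nor the within-couple intraclass correlation (ICC). Both are assumed below. For an analysis adjusted for baseline, the relevant ICC is that of the adjusted outcome.

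**Design effect.** In an arm of n people, c·n of them are in couples, which makes c·n/2 pairs. The variance of the arm total is

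nσ² + 2 × (c·n/2) × ICC × σ² = nσ²(1 + c × ICC).

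The design effect is therefore DE = 1 + c × ICC. If c is the same in every arm, it applies equally to a difference between arms.

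**True error of a nominal 5% two-sided test.** α = 2[1 − Φ(1.96/√DE)].

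| Share in couples | ICC | DE | 1.96/√DE | True α |
|---|---|---|---|---|
| 5% | 0.3 | 1.015 | 1.945 | 5.2% |
| 10% | 0.5 | 1.05 | 1.913 | 5.6% |
| 20% | 0.3 | 1.06 | 1.904 | 5.7% |
| 40% | 0.5 | 1.20 | 1.789 | 7.4% |
| 60% | 0.5 | 1.30 | 1.719 | 8.6% |

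**Effective sample size.** For outcomes measured in all arms, 120/1.06 = 113 and 120/1.30 = 92. Adherence exists only in the four exercise arms, about 4 × 24 = 96 people if arms are equal, so 96/1.06 = 91 and 96/1.30 = 74.

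**Multi-group tests.** The table describes a two-arm contrast. For an overall test, divide the chi-squared critical value by DE.

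- Five arms (4 df): 9.488/1.06 = 8.95, error about 6.2%. At 50% in couples and ICC 0.5, DE = 1.25 and 9.488/1.25 = 7.59, error about 10.8%. A simulation of five arms of 24 with an ordinary ANOVA also gave 10.8% for this second case.
- Four arms, as for adherence (3 df): 7.815/1.06 = 7.37, error about 6.1%; 7.815/1.30 = 6.01, error about 11.1%.

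The z-test figures are thus somewhat low for the overall tests.

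**The case against.** The strongest reply is that the allocation rule is conditional. It applies only if a couple takes part, and nothing in the article says how many will. With 5–10% of participants in couples the error stays at 5.2–5.6%, which is close to negligible, and the 8.6% figure needs 60% of the sample to be couples. The direction is not guaranteed either: leg-press strength in mixed-sex couples could correlate weakly or even negatively, and the plan adjusts for sex only if the groups differ on it. All of this stands. A reader might infer that the p-values are certain to be too small; the article supports that only under a positive correlation among couples who actually enrol.

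A reader might also infer a larger problem from class-based training. With fixed classes of 8 and an assumed ICC of 0.02–0.05, the design effect in SUP and SUP+ would be 1 + 7 × 0.02 = 1.14 to 1 + 7 × 0.05 = 1.35. The article caps attendance per session but does not say that people stay in one class or that classes have different instructors, and recruitment was expected to run from September 2022 to late 2024. Classes are not units of allocation. That stronger reading is not supported as a defect of the main analysis.

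Third, the cluster-trial reference could be a slip, or a sign that a fuller plan handles clustering. It does not show that clustering will be ignored. But the article does not leave the tests open. It names independent-observation tests after setting a household allocation rule, and that mismatch goes beyond what condensing a protocol explains.

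**Conclusion.** The point holds in conditional form. The allocation rule, the cited reporting standard and the named tests do not fit together. If couples enrol and their outcomes correlate positively, the planned tests understate standard errors.

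The size cannot be fixed from the article. Under the assumed values the z-test approximation gives a true error between 5.2% (few couples) and 8.6% (60% in couples, ICC 0.5), and the overall multi-group tests inflate somewhat more. Adherence is the outcome where a positive correlation is most plausible. With few couples the effect is small, so this should be corrected but does not by itself invalidate the trial.

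**What to change.** - **Repeated outcomes.** Replace the group-by-time ANCOVA with a linear mixed model that has a household random intercept, with people living without an enrolled partner as clusters of one, in addition to the within-person repeated measures. Alternatively, use standard errors that are cluster-robust at household level. If few couples enrol, the household variance will be poorly estimated, so name the fallback in advance.
- **Adherence, adverse events and dropouts.** Use household-clustered methods in place of plain ANOVA and chi-squared tests, for example GEE with a small-sample correction. The correction matters with about 24 people per arm and possibly sparse events.
- **Wording.** State that allocation is individual except for cohabiting couples, reconcile this with the cluster-trial reference, and report the number of couples per arm.
- **Classes.** Examine clustering by supervised class, in SUP and SUP+ only, as a sensitivity analysis if class membership proves stable.

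The cost is more than a wording change, because the planned ANCOVA has no place for a household intercept and must be replaced. No new data are needed beyond a household identifier, which the allocation rule already requires. Intervals become slightly wider.

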### Trial groups

All participants allocated to exercise intervention groups will complete a 24-week multicomponent exercise program consisting mostly of resistance exercises (3 sessions per week; 60 min per session). The exercise program will be reported following the Consensus on Exercise Reporting Template (CERT) [38] (see Supplementary Table 2). After completing the baseline assessment, participants will be randomly allocated to the 5 study groups. After randomization and irrespective of intervention group allocation, a member research team member will inform the participant about the intervention and assessment plan.

The exercise program for all intervention groups will be divided into 3 difficulty levels, increasing every 8 weeks. Each will include 3 sessions comprising of warm-up, balance, resistance, aerobic, and flexibility exercises (Tables 1 and 2). Further information about the training variables is available in Supplementary Table 3.

**Table 1 Tab1:** Supervised exercise program

	**Session nº**	**Exercise nº**	**Intensity report**	**LEVEL 1**	**LEVEL 2**	**LEVEL 3**	**Type**
WARM-UP	1, 2 & 3	1	-	Seated ankle circumduction			Joint mobility
		2	-	Knee flexo-extension			
		3	-	Hip circumduction			
		4	-	Forward–backward shoulder circumduction			
		5	-	Wrist circumduction			
		6	-	Neck mobility			
		7	-	Diagonal foot touches	Foot touches forward, to the side and back with hands on the waist	Foot touches forward, to the side and back with arms in cross position	Balance
		8	-	Heel lifts	One leg balance	One leg balance with arms in cross position	
		9	-	Lateral movement without impact	Lateral movement with impact	Rope skipping	Soft cardio
		10	-	´V´ front	Knee-elbow	Low skipping	
MAIN ACTIVITY	1	1	-	One leg balance with arms in cross position	One leg balance with leg abduction	One leg balance with shoulder flexion	Balance
		2	RIR	Machine chest press	Cable crossover	Dumbbell chest press	UB push (pectoral, triceps)
		3	RIR	Box squat	Goblet squat	Jump squat	LB (quadriceps, gluteus)
		4	RIR	Pulley shoulder flys	Alternating dumbbells shoulder flys	Simultaneous dumbbells shoulder flys	UB pull (trapezius, deltoid)
		5	RIR	Assisted TRX lunge	Lunge	Weighted lunge	LB (quadriceps, gluteus)
		6	RPE	Front plank with shoulder touches	Front plank with knees	Front plank	Core
		7	RIR	Seated rowing machine	Standing cable row (medium height)	Unilateral dumbbell row	UB pull (dorsal)
		8	RIR	Knee-banded seated hip abduction	Monster walk	Clamshell	LB (gluteus)
		9	RPE	Lateral movements	Jumping jacks	Side-to-side shuffle	Cardio
		10	RPE	Bike or elliptical	Step machine	Running	
	2	1	-	Foot touches forward, to the side and back with hands on the waist	Foot touches forward, to the side and back with arms in cross position	Foot touches forward, to the side and back with arm movements at the same level	Balance
		2	RIR	Seated dumbbell shoulder press	TRX pendulum press	Standing barbell shoulder press	UB push (deltoid)
		3	RPE	Bird dog	Unilateral bird dog	Alternating bird dog with abduction	Core
		4	RIR	Pulley facepull	Pulley facepull with external rotation	Assisted scapular pull up	UB pull (trapezium, rhomboids)
		5	RIR	Leg press with external foot rotation	Multipower sumo squat	Weighted sumo squat	LB (quadriceps, gluteus)
		6	RPE	Pulley lateral rotation	Dynamic kneeling side plank	Static kneeling side plank	Core
		7	RIR	Standing cable row (high pulley)	Standing unilateral cable row (high pulley)	Standing cable pullover (high pulley)	UB pull (dorsal)
		8	RIR	Glute bridge	Hip thrust	Unilateral hip thrust	LB (gluteus)
		9	RPE	Slow climber	Beginner burpee	Beginner burpee with jump	Cardio
		10	RPE	Bike or elliptical	Step machine	Running	
	3	1	-	One leg balance with knee elevation	One leg balance with knee elevation and external rotation	One leg balance with hip extension and external rotation	Balance
		2	RIR	Pulley triceps extension	Dumbbell triceps kickback	Unilateral overhead triceps extension	UB push (triceps)
		3	RIR	Step up (alternative)	Step up (same leg)	Bulgarian squat with support	LB (quadriceps, gluteus)
		4	RIR	Pull down	Unilateral pull down	Machine assisted pull up	UB pull (dorsal, biceps)
		5	RPE	Isometric wall squat	Dynamic unilateral isometric wall squat	Static unilateral isometric wall squat	LB (quadriceps)
		6	RPE	Press pallof with elastic	Press pallof with elastic and disc	Pulley pallof press	Core
		7	RIR	Standing biceps cable curl	Alternating standing dumbbell biceps curl	Simultaneous standing dumbbell biceps curl	UB pull (biceps)
		8	RIR	Pull throught	Kettlebell deadlift	Barbell deadlift	LB (quadriceps, gluteus)
		9	RPE	Low skipping	Medium skipping	High skipping	Cardio
		10	RPE	Bike or elliptical	Step machine	Running	
COOL-DOWN	1, 2 & 3	1	-	Calf stretch	Dorsal stretch	Back stretch	Flexibility
		2	-	Chair hamstring stretch	Biceps and pectoral stretch	Pectoral stretch on the floor	
		3	-	Gluteus stretch	Deltoid stretch	Hamstring stretch with elastic	
		4	-	Quadriceps stretch with support	Lying quadriceps stretch	Psoas stretch	
		5	-	Back stretch with support	Standing hamstring stretch	Soleus stretch	
		6	-	Pectoral wall stretch	Neck stretch	Forearm stretch	
		7	-	Neck stretch	Adductor stretch	Seated gluteus stretch	

*LB* Lower-body, *RIR* Repetitions in reserve, *RPE* Rate of perceived exertion, *UB* Upper-body

**Table 2 Tab2:** Unsupervised exercise program

	**Session nº**	**Exercise nº**	**Intensity report**	**LEVEL 1**	**LEVEL 2**	**LEVEL 3**	**Type**
WARM-UP	1, 2 & 3	1	-	Seated ankle circumduction			Joint mobility
		2	-	Knee flexo-extension			
		3	-	Hip circumduction			
		4	-	Forward–backward shoulder circumduction			
		5	-	Wrist circumduction			
		6	-	Neck mobility			
		7	-	Diagonal foot touches	Foot touches forward, to the side and back with hands on the waist	Foot touches forward, to the side and back with arms in cross position	Balance
		8	-	Heel lifts	One leg balance	One leg balance with arms in cross position	
		9	-	Lateral movement without impact	Lateral movement with impact	Rope skipping	Soft cardio
		10	-	´V´ front	Knee-elbow	Low skipping	
MAIN ACTIVITY	1	1	-	One leg balance with arms in cross position	One leg balance with leg abduction	One leg balance with shoulder flexion	Balance
		2	RIR	Wall push-ups	Quadruped push-ups	Knee push-ups	UB push (pectoral, triceps)
		3	RIR	Chair squat	Squat with elastic	Jumping squat	LB (quadriceps, gluteus)
		4	RIR	Vertical rowing with elastic	Alternating shoulder flys with elastic	Simultaneous shoulder flys with elastic	UB pull (trapezius, deltoid)
		5	RIR	Lunge with support	Lunge	Lunge with elastic	LB (quadriceps, gluteus)
		6	RPE	Front plank with shoulder touches	Front plank with knees	Front plank	Core
		7	RIR	Seated rowing with elastic	Simultaneous standing rowing with elastic	Unilateral standing rowing with elastic	UB pull (dorsal)
		8	RIR	Knee-banded seated hip abduction	Monster walk	Clamshell	LB (gluteus)
		9	RPE	Lateral movements	Jumping jacks	Side-to-side shuffle	Cardio
		10	RPE	Kneeling on the spot	Alternating step-up	Simultaneous step-up	
	2	1	-	Foot touches forward, to the side and back with hands on the waist	Foot touches forward, to the side and back with arms in cross position	Foot touches forward, to the side and back with arm movements at the same level	Balance
		2	RIR	Seated shoulder press with elastic	Unilateral seated shoulder press with elastic	Standing shoulder press with elastic	UB push (deltoid)
		3	RPE	Bird dog	Unilateral bird dog	Alternating bird dog with abduction	Core
		4	RIR	Scapular retraction with elastic	Alternating scapular retraction with elastic	Scapular retraction lying with elastic	UB pull (trapezium, rhomboids)
		5	RIR	Sumo chair squat	Sumo squat	Sumo squat with elastic band	LB (quadriceps, gluteus)
		6	RPE	Kneeling side plank	Kneeling side plank with leg abduction	Lateral rotation with elastic	Core
		7	RIR	Seated rowing with elastic	Simultaneous standing rowing with elastic	Unilateral standing rowing with elastic	UB pull (dorsal)
		8	RIR	Glute bridge with elastic	Frog pump with elastic	Unilateral glute bridge with elastic	LB (gluteus)
		9	RPE	Slow climber	Beginner burpee	Beginner burpee with jump	Cardio
		10	RPE	Kneeling on the spot	Alternating step-up	Simultaneous step-up	
	3	1	-	One leg balance with knee elevation	One leg balance with knee elevation and external rotation	One leg balance with hip extension and external rotation	Balance
		2	RIR	Seated triceps extension with elastic	Triceps kickback with elastic	Unilateral overhead triceps extension with elastic	UB push (triceps)
		3	RIR	Lunge with support	Lunge	Lunge with elastic	LB (quadriceps, gluteus)
		4	RIR	Scapular retraction with elastic	Pull with elastic	Alternating pull with elastic	UB pull (dorsal, biceps)
		5	RPE	Isometric wall squat	Dynamic unilateral isometric wall squat	Static unilateral isometric wall squat	LB (quadriceps)
		6	RPE	Dead bug with leg movements	Dynamic dead bug	Static dead bug	Core
		7	RIR	Seated biceps curl with elastic	Alternating standing biceps curl with elastic	Simultaneous standing biceps curl with elastic	UB pull (biceps)
		8	RIR	Sumo deadlift with elastic	Conventional deadlift with elastic	Unilateral conventional deadlift with elastic	LB (quadriceps, gluteus)
		9	RPE	Low skipping	Medium skipping	High skipping	Cardio
		10	RPE	Lateral movements	Jumping jacks	Side-to-side shuffle	
COOL-DOWN	1, 2 & 3	1	-	Calf stretch	Dorsal stretch	Back stretch	Flexibility
		2	-	Chair hamstring stretch	Biceps and pectoral stretch	Pectoral stretch on the floor	
		3	-	Gluteus stretch	Deltoid stretch	Hamstring stretch with elastic band	
		4	-	Supported quadriceps stretch	Lying quadriceps stretch	Psoas stretch	
		5	-	Back stretch with support	Standing hamstring stretch	Soleus stretch	
		6	-	Pectoral wall stretch	Neck stretch	Forearm stretch	
		7	-	Neck stretch	Adductor stretch	Seated gluteus stretch	

*LB* Lower-body, *RIR* Repetitions in reserve, *RPE* Rate of perceived exertion, *UB* Upper-body

*1- Control group (CON)*

Participants will not perform any other exercise program during the intervention period and will be advised to maintain their usual lifestyle.

*2- Supervised exercise without motivational intervention (SUP)*

The SUP group will participate in an exercise program conducted at university facilities in small groups (≤ 8 participants per session) under the supervision of a sports scientist. The program will be conducted with the equipment usually available at a gym (*i.e.,* weight machines, dumbbells, kettlebells, discs, pulleys, elastic bands, and stationary bicycles).

*3- Supervised exercise with motivational intervention (SUP +)*

The SUP + group will receive the same exercise program as the SUP group (Table 1) but with motivational strategies based on self-determination theory designed to increase participants’ perception of autonomy, competence, and relatedness. These strategies will be based on 6 colors simulating martial arts levels, from white belt (beginner) to black belt (advanced). Each level will employ different strategies to achieve the specific objectives set for that level. Motivational strategies include telephone calls, educational infographics, workshops and videos about exercise benefits, motivational messages before and after each training session, and reports of the results obtained in the mid-intervention assessment. More details about the motivational strategies are available in Supplementary Table 4.

*4- Unsupervised exercise without motivational intervention (UNSUP)*

The UNSUP group will complete an unsupervised exercise program prescribed via a mobile app designed for at-home use without face-to-face supervision. The program will involve exercises that target the same muscle groups and movements as the supervised groups but are adapted to be performed at home using elastic bands and participants’ body weight.

*5- Unsupervised exercise with motivational intervention (UNSUP +)*

The UNSUP + group will receive the same exercise program as the UNSUP group (as detailed in Table 2), plus equivalent motivational strategies to those administered to the SUP + group. More information is available in Supplementary Table 4.

At the end of the 24-week intervention, all participants (including those in the CON group) will be provided with elastic bands and a list of training centers supervised by sports scientists (including a discount on some of them). Thus, they will have equal opportunities to engage in the exercise practice that best suits their circumstances, preferences, tastes, and interests.

